### Monitoring and quality control

Adherence to study protocols will be monitored by random visits to the clinic sites and the communities where preliminary screening takes place. The investigators will review all case report forms before data entry to ensure completeness. Protocol deviations, defined as variations from the IRB-approved protocol, will be fully documented, including corrective measures taken, and will be reported to the DMEC and the IRBs approving the study protocol.

All team members are trained thoroughly on study procedures, as documented by the training log. Investigators visit the field biweekly to review the performance of staff. Retraining and orientation are provided every six months.

## Data management and analysis plan

Data will be collected on paper forms initially and then entered into an electronic database developed in Microsoft Access (Microsoft Corporation, Redmond, Washington, USA) at the data centre at Gullapalli Pratibha Rao International Centre for Advancement of Rural Eye care in Hyderabad, Telangana, India. Data will be securely stored in encrypted cloud-based institute servers. Personal data will be stored in a different database with access restricted to primary investigators. Data will be analysed at the end of the trial when all follow-up assessments are completed. All randomised participants will be assessed based on the intention-to-treat principle in the main analysis. Per-protocol analysis will also be conducted as secondary analysis, analysing participants according to treatment they actually received. No formal interim analysis will be done for the primary outcome measure.

Baseline characteristics and follow-up measurements will be summarised as mean and standard deviation, median and inter-quartile range, or numbers and frequencies (%) as appropriate, depending on the scale and distribution of measurements. Histograms or Q-Q plots will be used to assess the normality of all continuous variables.

Global cognitive factor scores for our study population will be calculated using the cognitive test data from the LASI-DAD battery. This calculation is similar to that performed in the ACHIEVE trial, which investigated the impact of hearing aids on cognitive decline [33]. In ACHIEVE, the global cognitive factor score was the primary outcome measure calculated using the ARIC (Atherosclerosis Risk in Communities) cognitive battery [33]. The between-group difference in three-year change in LASI-DAD global cognitive score (primary outcome) will be calculated. A linear mixed-model regression analysis with restricted maximum likelihood estimation will be used to assess between-group differences in change in LASI-DAD global cognitive score over time after adjusting for potential confounders (baseline cognitive score, age, sex, education, visual function, quality of life, depression, falls, social interaction, and physical activity).

Three-year change from baseline in quality of life, visual functioning, depression, falls, social interaction and networking, and physical activity will be the secondary outcomes. Rasch analysis will be conducted to derive interval scores from quality of life and vision-related quality-of-life instruments. A mixed-effects binomial regression with a log link will be used to estimate the relative risk, and a binomial model with an identity link for estimating the risk difference will be used to assess between-group differences in change in depression. A mixed-effects linear regression with an identity link will be used to estimate the between-group mean difference in change in falls. Participants will be placed into three categories of physical activity and social interaction for these analyses as previously described [30, 34].

The cost-effectiveness analysis will estimate the expected incremental cost per unit difference in the cognitive factor scores between the intervention and the control groups. A health and social care perspective will be used for the analysis. A Markov model will be developed, allowing the comparison of the CLEVER intervention with alternative interventions for preventing cognitive decline. An “in-trial” analysis that compares the costs and outcomes of the two study groups for the time horizon of the trial will be conducted. Multinomial logistic regression will be used to adjust for potential confounders. Odds ratios and their 95% confidence intervals will be reported.

Statistical significance of all results will be assessed at the conventional level of *p* < 0.05 (two-tailed). Stata (V.16, Stata Corp, College Station, Texas, USA) will be used for all statistical analyses.

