### Trial design

CLEVER is a single-centre, open-label, parallel-group, individually-randomised controlled trial, designed to test the impact of immediate versus delayed provision of free spectacles on rates of cognitive change among community-dwelling elderly persons.

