### Sample size

Based on the three-year, un-intervened decline in LASI-DAD (Longitudinal Aging Study in India–Diagnostic Assessment of Dementia) global cognitive score from a cross-sectional study of similarly aged persons in India [23, 24], with 90% power at *p* = 0.05 (two-tailed) using a two-sample t-test and estimated annual follow-up loss of 13% based on our other studies in this demographic group in the region, 760 participants across the two study groups are sufficient to detect a 29% effect size. Using a conservative estimate that 10% of screened persons will be eligible, an estimated 7600 will need to be screened to recruit 760 participants.

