### Intervention

All participants in the intervention group will receive free near and/or distance spectacles plus instructions on their use within two weeks of the examination, with annual replacement in case of loss, breakage or change in power such that VA falls below the enrolment criteria. Adherence with use of spectacles will be assessed in both study groups through phone calls made every three months and half yearly home visits. Intervention group participants adherent with spectacle wear will be rewarded through nonfinancial incentives such as vouchers for diagnostic tests and other utility items at regular intervals. There will be no special criteria for discontinuing or modifying allocated interventions. No attempts will be made to prevent control participants from obtaining spectacles outside the study based on the prescriptions provided.

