### Controls

All participants randomised to the control group will receive a prescription for spectacles at baseline, as is the standard of care in the area, and will receive near and/or distance spectacles at no cost at study closeout.

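### The secondary analysis is labelled per-protocol but defined by treatment received, which is an as-treated comparison that can move participants out of their randomised arm

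*Protocol article*

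**What the plan says.** All references are to the protocol article; no separate statistical analysis plan is at hand.

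- **Data management and analysis plan**, main analysis: "All randomised participants will be assessed based on the intention-to-treat principle in the main analysis".
- **Same section**, secondary analysis: "Per-protocol analysis will also be conducted as secondary analysis, analysing participants according to treatment they actually received". It gives no adherence criterion, no exclusion rule and no list of deviations that would remove a participant. No other section defines the analysis differently.
- **Controls**: "All participants randomised to the control group will receive a prescription for spectacles at baseline". Free spectacles follow at study closeout.
- **Intervention**: "No attempts will be made to prevent control participants from obtaining spectacles outside the study based on the prescriptions provided".
- **Intervention**, on measurement of use: "Adherence with use of spectacles will be assessed in both study groups through phone calls made every three months and half yearly home visits". Adherent intervention participants are rewarded with vouchers and other items.
- **Trial design**: "CLEVER is a single-centre, open-label, parallel-group, individually-randomised controlled trial". The contrast is immediate against delayed provision of free spectacles.

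**The concern.** The label and the definition name two different analyses. Per-protocol means comparing the randomised arms among those who followed their allocation. Analysing by treatment received means forming new groups that randomisation did not create. An analysis plan that follows this sentence has to break either the label or the definition.

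The difference matters here because switching is built into the design: controls have a prescription and are free to act on it. A control who does so may be counted as treated. Whoever obtains or uses spectacles may differ in income, education or cognitive reserve, all of which could bear on cognitive change. The Background justifies the trial on the ground that only an experimental design can establish cause and effect. A regrouped comparison goes back to an observational contrast, and readers who see it called per-protocol may not notice.

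**Working it through.** **1. The plan's own figure.** Inputs from Sample size and the Abstract: 90% power, two-sided 0.05, two-sample t-test, 13% annual loss, 29% effect, 760 in total (380 per arm). No SD is stated, so 29% is read as a standardised difference of 0.29.

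- Per arm: n = 2 × (1.960 + 1.282)² / 0.29² ≈ 250, so 500 in total.
- Three-year retention: 0.87³ = 0.6585, a loss of 34.15%.
- 500 / 0.6585 = 759.3, rounded up to 760.

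The stated number is reproduced, and nothing in this point changes it. About 250 completers per arm are expected.

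**2. Label against definition.**

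| | Grouping | Who is analysed |
|---|---|---|
| Intention to treat (main) | randomised arm | all randomised |
| Per-protocol, usual meaning | randomised arm | compliers only |
| As written in the plan | treatment received | no restriction stated |

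The third row is as-treated. This is a definition the article states, not a detail left for later.

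**3. Illustration of size.** Every input in this step is an assumption, because the documents give no uptake or wear rates.

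- The true effect is zero and the comparison is unadjusted.
- Received is taken to mean worn.
- A share q of the intervention arm does not wear spectacles, and the same share q of controls does.
- Wear follows one standard normal trait in both arms, which correlates r with cognitive change (outcome SD 1).

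Let φ be the normal density at the q quantile. Half of all participants wear spectacles. The mean trait is +2φ in wearers and −2φ in non-wearers, so:

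- as-treated difference = 4φ × r
- compliers within randomised arms = 2φ / (1 − q) × r
- intention to treat = 0

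| q | φ | r | As-treated | Share of 0.29 | Within-arm compliers |
|---|---|---|---|---|---|
| 10% | 0.1755 | 0.1 | 0.070 | 24% | 0.039 |
| 10% | 0.1755 | 0.2 | 0.140 | 48% | 0.078 |
| 20% | 0.2800 | 0.1 | 0.112 | 39% | 0.070 |
| 20% | 0.2800 | 0.2 | 0.224 | 77% | 0.140 |

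A simulation on a wider assumed grid (10–30% control uptake, 0–20% non-wear, r of 0.2–0.3) gave as-treated differences of 0.07 to 0.38 SD and within-arm differences of 0.04 to 0.25 SD. Intention to treat stayed at about zero. The as-treated bias was the larger of the two in every scenario.

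**4. Precision of the instrumental estimate.** The complier-average effect divides the intention-to-treat difference by the between-arm difference in wear, 1 − 2q. Its standard error is therefore roughly 1/0.8 = 1.25 times the intention-to-treat one at q = 10%, and 1/0.6 = 1.67 times at q = 20%.

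**The case against.** Several objections limit how far this goes.

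- **The analysis is only secondary.** Intention to treat is the main analysis for all randomised participants, so the primary estimate and its type I error are untouched. This stands. A reader might infer that the regrouped result would be put forward if the main result is null; nothing in the documents supports that prediction.
- **Received need not mean worn.** Trial design frames the contrast as provision of free spectacles, and Intervention treats wear separately as adherence. On that reading a non-wearer who was given spectacles stays treated, and a control who buys a pair has arguably not had the trial treatment. Regrouping could then be much smaller than in the illustration. This stands against the size, but not against the mismatch: on either reading the groups are formed by receipt and not by allocation.
- **The calculation is crude.** The planned mixed model adjusts for baseline cognitive score, age, sex and education. Whether it also applies to this secondary analysis is not said. If it does, r must be read as the correlation left after adjustment. Some confounding could remain: income is collected at baseline (Table 1) but is not among the listed covariates.
- **False-positive rates.** With 250 wearers against 250 non-wearers the standard error is √(2/250) = 0.089. A reader might turn the four rows into rejection probabilities of about 12%, 35%, 24% and 71%. The arithmetic is right, but these are not error rates of the planned analysis. They rest on assumed rates and correlations, one shared trait in both arms, regrouping by wear, and no adjustment.
- **The usual per-protocol analysis is biased too.** This stands, as the last column of the table shows. Correcting the label alone gives no causal estimate.
- **The instrumental estimate has its own assumption.** Allocation must affect cognition only through wear. Vouchers for diagnostic tests and other items go to adherent intervention participants, and the trial is open-label; both strain that assumption. So it is a preferred option, not the only acceptable one.

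**Conclusion.** The point holds as an error in the article's own wording. The secondary analysis is called per-protocol and defined as as-treated, in a trial where controls can obtain the intervention themselves. Followed literally, the plan would report a non-randomised comparison, open to confounding, under a label that suggests otherwise.

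That conclusion needs no numerical assumption. The size does: 0.07–0.22 SD against a 0.29 SD design effect is an illustration of what is possible, not an estimate of what this trial will show. The documents do not support a claim that the trial's main conclusion is at risk, nor any particular false-positive rate. The correction should be made because it costs little and the spectacle-use data it needs are already planned in both arms.

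**What to change.** Replace the sentence so that label and method agree and the randomised comparison is kept where possible.

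**Preferred.** Suggested text: *As a secondary analysis, the effect of wearing spectacles will be estimated as a complier-average causal effect, with randomised arm as the instrument and adjustment for baseline covariates. Wear will be defined, before data are analysed, from the three-monthly calls and half-yearly visits in both arms. The exclusion restriction will be stated, with discussion of how adherence vouchers and the open-label design may strain it.*

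**Alternative.** Define a per-protocol set within the randomised arms by a pre-specified adherence criterion. Adjust for baseline predictors of adherence, including income, and acknowledge the remaining selection bias.

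**If the treatment-received analysis is kept.** Call it as-treated, non-randomised and exploratory. State whether received means supplied or worn, and how a control's own purchase is classified.

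**Cost.** One sentence in the protocol, a rule that turns repeated use records into a wear variable, and a little more analysis. No new data are needed. The complier-average interval will be wider, by a factor of roughly 1.25 to 1.67 relative to intention to treat under the assumed 10–20% crossover in each arm.

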**Methods:**

Cognitive Level Enhancement through Vision Exams and Refraction (CLEVER) is a single-centre, open-label, parallel-group, individually-randomised trial. Participants (760 total, 380 in each arm) aged ≥ 60 years with correctable vision impairment at distance and/or near (presenting visual acuity < 6/18 in the better-seeing eye and improving to > = 6/18 with spectacles and/or presenting near vision worse than N6 at 40 cm and improving to N6 with spectacles), normal hearing (able to repeat at least three out of six words whispered from a 50 cm distance in the better ear) and normal cognition (Hindi Mini-mental Status Examination score > 18/31) will be enrolled. After a comprehensive eye examination, intervention group participants will receive distance, near, or bifocal spectacles, while controls will receive a prescription and spectacles at the end of the trial. The primary outcome will be the three-year change in Longitudinal Aging Study in India–Diagnostic Assessment of Dementia (LASI DAD) global cognitive factor score, with and without adjustment for baseline score, age, gender, education and other potential confounders.

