Observational studies have consistently found a positive association between vision impairment and cognitive decline [18]. The hypothesized pathways through which VI may influence cognitive health include increases in social isolation, physical inactivity, depression and changes in brain structure and increased cognitive load [5]. However, only experimental interventional study designs, such as randomised controlled trials (RCTs), can establish a cause-and-effect relationship between vision care and cognitive change. No such trials have yet been done.

The Cognitive Level Enhancement through Vision Exams and Refraction (CLEVER) trial aims to assess the impact of spectacles for distance and/or near vision correction on cognitive change among community-dwelling elderly persons in Telangana, India, over three years. This trial also seeks to understand the cost-effectiveness and impact of near and distance spectacles on quality of life, falls, depression, social interaction, and physical activity among study participants. The current report describes the CLEVER trial protocol.

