### Secondary outcomes

These include 36-month change in quality of life using the World Health Organization Quality of Life Brief Version (WHOQOL-BREF) [27], visual functioning (21-item Rasch version of the Indian Vision Function Questionnaire) [28], depression (Patient Health Questionnaire-9) [29], physical activity (International Physical Activity Questionnaire) [30], social interaction and networking (Social Networking Index questionnaire) [24], and falls risk (Quick Screen falls assessment) [31]. The trial will also assess the cost-effectiveness of the intervention as total intervention cost per quality-adjusted life years gained in the intervention group. The Client Service Receipt Inventory will be used to assess the resource use for medical care by the study participants [32] (Table 1).

**Table 1 Tab1:** Schedule of assessments with details on location, personnel, and frequency

	Instrument name	Details	Baseline	Year 1	Year 2	Year 3
1	Personal and demographic information questionnaire	It includes age/gender, level of education, marital status, and income	✓			
2	World Health Organization Quality of Life Brief Version (WHOQOL-BREF) [27]	It has 26 items and covers four domains of quality of life: a) physical health, b) psychological well-being, c) social relationships, and d) environment	✓	✓	✓	✓
3	Indian Vision Function Questionnaire [28]	It has 20 questions covering visual functioning and mobility domains	✓	✓	✓	✓
4	Patient Health Questionnaire (PHQ9) for depression [29]	It has nine questions with scores of 0–3 points per question, for a total score of 0–27 points	✓	✓	✓	✓
5	Social Networking Index questionnaire [24]	It has 12 questions that assess the number of high-contact roles (network diversity), number of people in social networks, and embedded networks	✓	✓	✓	✓
6	International Physical Activity Questionnaire (IPAQ) Short form [30]	It has 7 questions and measures a 7-day recall of physical activities	✓	✓	✓	✓
7	Risk factors (alcohol consumption and smoking)	Includes questions on present and past smoking and alcohol consumption	✓	✓	✓	✓
8	Hindi Mini mental State Examination (HMSE) [19]	It is a 22 questions-based scale with a maximum score of 31	✓			
9	Ocular history and systemic health questionnaire	It includes questions on previous surgeries, use of spectacles, and duration of use. Systemic health questionnaire includes information on hypertension, diabetes and other non-communicable diseases	✓	✓	✓	✓

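### The adjusted model for the primary outcome includes six of the trial's own secondary outcomes as confounders, without limiting them to baseline values or saying whether it is the primary analysis

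*Protocol article*

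**What the plan says.** The only regression model that the protocol article describes for the primary outcome is in the section Data management and analysis plan. It is a linear mixed model fitted by REML, used to assess "between-group differences in change in LASI-DAD global cognitive score over time after adjusting for potential confounders". The covariates in brackets are "baseline cognitive score, age, sex, education, visual function, quality of life, depression, falls, social interaction, and physical activity". The sentence before it says that the between-group difference in three-year change, labelled the primary outcome, will be calculated.

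The same section then states: "Three-year change from baseline in quality of life, visual functioning, depression, falls, social interaction and networking, and physical activity will be the secondary outcomes". The Background makes it an aim to study the "impact of near and distance spectacles on quality of life, falls, depression, social interaction, and physical activity among study participants", and says that the hypothesised routes from vision impairment to cognition "include increases in social isolation, physical inactivity, depression and changes in brain structure and increased cognitive load". Table 1 schedules the six corresponding instruments at baseline and at years 1, 2 and 3.

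The abstract says that the primary outcome will be analysed "with and without adjustment for baseline score, age, gender, education and other potential confounders". The sample size section bases its 90% power on a two-sample t-test.

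**The concern.** The six variables cannot simply be taken as confounders of a randomised comparison. Randomisation removes confounding of the assigned groups in expectation, and the protocol itself treats these variables as things that spectacles may change. Their baseline values are harmless covariates and may add precision. Their follow-up values are consequences of allocation. A model that conditions on them removes whatever part of the effect passes through them. It can also introduce collider bias where an unmeasured factor affects both, say, depression and cognition.

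The covariate list attaches the word baseline to the cognitive score alone. A mixed model of annual scores readily takes time-varying covariates, and follow-up values will exist for all six. The text therefore allows two models with different estimands, and only one of them answers the trial's question about providing spectacles. Because no analysis is named as primary, the choice among the unadjusted result and the two adjusted versions could be made after the results are known.

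**Working it through.** **1. Matching the lists.**

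| Covariate in the model | Secondary outcome | Named pathway (Background) | Measured (Table 1) |
|---|---|---|---|
| Visual function | yes | no | baseline, years 1–3 |
| Quality of life | yes | no | baseline, years 1–3 |
| Depression | yes | yes | baseline, years 1–3 |
| Falls | yes | no | baseline, years 1–3 |
| Social interaction | yes | yes (social isolation) | baseline, years 1–3 |
| Physical activity | yes | yes (physical inactivity) | baseline, years 1–3 |

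Six of six are secondary outcomes, and three of six correspond to named pathways. The falls instrument also counts vision among its components (Table 1). Baseline HMSE, a stratification factor, is not in the covariate list.

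**2. Reproducing the sample size.** Inputs from the sample size section: two-sided alpha 0.05, power 90%, annual loss 13%, 29% effect size. I read the last as a standardised difference d = 0.29, which is an assumption.

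- Completers per arm: 2 × (1.960 + 1.282)² / 0.29² = 249.9, so 250.
- Three-year retention: 0.87³ = 0.6585.
- Recruited per arm: 250 / 0.6585 = 379.7, so 380, and 760 in total.

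This matches the stated figure exactly. A version based on the noncentral t distribution gives 251 per arm and 764 in total. The trial is therefore sized for the total effect, in an unadjusted comparison.

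**3. If follow-up values are entered.** Let f be the share of the total effect carried by the adjusted variables. The document gives no value for f, so a range is shown. The model then targets 0.29 × (1 − f). With 250 per arm and SD 1, power = Φ(0.29 × (1 − f) × √(250/2) − 1.96).

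| f (assumed) | Targeted d | Power |
|---|---|---|
| 0% | 0.290 | 90% |
| 10% | 0.261 | 83% |
| 25% | 0.218 | 68% |
| 50% | 0.145 | 37% |
| 75% | 0.073 | 12.5% |

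For f = 50%, for example: 0.145 × 11.18 − 1.96 = −0.339, and Φ(−0.339) = 0.367.

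**4. Baseline against follow-up values, by simulation.** 3,000 runs, 250 per arm, total effect 0.29. There is one intermediate variable, which spectacles shift by 0.5 SD and which has correlation 0.5 with its own baseline within arm (both assumed). Each cell gives the mean estimate and the power.

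| f | No adjustment | Baseline value | Follow-up value |
|---|---|---|---|
| 25% | 0.289; 0.89 | 0.289; 0.89 | 0.217; 0.66 |
| 50% | 0.289; 0.89 | 0.288; 0.90 | 0.144; 0.37 |
| 75% | 0.286; 0.90 | 0.286; 0.91 | 0.069; 0.13 |

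Baseline adjustment leaves the estimate and the power intact, while follow-up adjustment removes the mediated share. The simulation uses a single three-year comparison, not the full longitudinal model. It contains no unmeasured common cause, so it shows attenuation only and says nothing about collider bias.

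**The case against.** The strongest reply is that the document nowhere says that follow-up values will be used. The list opens with four pre-randomisation variables, the word baseline may be meant to govern all of it, and potential confounders usually means baseline characteristics. A mixed model does not require time-varying covariates, and their timing is often left to the analysis plan. All of this is fair, and a reader who infers that the model will condition on follow-up values goes beyond the text. What remains is that the protocol does fix a covariate list, that the list consists in large part of outcomes, and that its wording permits the harmful version.

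A reader might also infer that the stated 90% power is lost. The document does not support this. The power belongs to a two-sample t-test, the abstract plans an unadjusted analysis, and that comparison keeps its power whatever enters the adjusted model. An estimate of the total effect will therefore exist. This limits the harm but does not remove it, because nothing says which result decides the trial.

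Two further readings go too far. The six variables are not all hypothesised pathways: the Background covers depression, social isolation and physical inactivity, while visual function, quality of life and falls are outcomes only. Nor is bias towards no effect certain: attenuation is to be expected if the pathways work as hypothesised, but collider bias can go in either direction.

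**Conclusion.** The point holds in a conditional form. The covariate list of the adjusted model contains six secondary outcomes without restricting them to baseline, and neither the adjusted nor the unadjusted analysis is designated primary. If baseline values are meant, there is no attenuation and only the wording needs repair. If follow-up values were entered, the adjusted model would not estimate the effect of providing spectacles. With an assumed 25% to 50% of the effect passing through these variables, it would target about 0.22 to 0.145 SD in place of 0.29, with power of about 68% to 37% in place of 90%. These figures rest on reading the 29% effect size as d = 0.29, on 250 completers per arm, and on a mediated share that the document does not give. They illustrate the risk and do not predict the result.

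**What to change.** State in the protocol and the analysis plan, before any outcome data are analysed, that:

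- the primary model uses pre-randomisation covariates only: baseline cognitive score and the stratification factors (age, sex, education and baseline HMSE), with any of the six other variables at baseline value only;
- this model is the single primary analysis, and the unadjusted comparison is supportive;
- any adjustment for follow-up values of the six variables belongs to a separately labelled exploratory mediation analysis.

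The term potential confounders is better replaced by baseline covariates. The change takes a few sentences. All the baseline measurements are already in Table 1, so it needs no new data, adds no participant burden and leaves the sample size as it is. Settling it early matters the more because the trial is open-label.

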### Randomisation, allocation and masking

The randomisation sequence will be generated by the trial statistician in the LVPEI CTU using an online randomisation tool (https://www.sealedenvelope.com). Stratified randomisation will be done based on gender (male/female), age (below and above median), education level (below and above median), and baseline HMSE (below and above median). Group allocation will be concealed from the trial coordinator and field team until a potential participant is determined eligible. Trial personnel will not be masked to participants’ treatment assignment due to practical difficulties in assessing the main trial outcome without study spectacles being worn. Masking of participants with use of zero-power spectacles among controls is not considered ethical in this setting.

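### For secondary outcomes analysed as scores, the plan names change from baseline and no own-baseline covariate; adding that covariate would gain precision at almost no cost

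*Protocol article*

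**What the plan says.** The secondary analyses are set out in the Protocol article under Data management and analysis plan: "Three-year change from baseline in quality of life, visual functioning, depression, falls, social interaction and networking, and physical activity will be the secondary outcomes". The models then differ by outcome.

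- **Falls:** "A mixed-effects linear regression with an identity link will be used to estimate the between-group mean difference in change in falls".
- **Depression:** a mixed-effects binomial model with a log link gives relative risks. A second model is described thus: "a binomial model with an identity link for estimating the risk difference will be used to assess between-group differences in change in depression".
- **Physical activity and social interaction:** "Participants will be placed into three categories of physical activity and social interaction for these analyses as previously described".
- **Quality of life and visual functioning:** Rasch-derived interval scores, with no between-group model named.

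No covariate is listed for any of these. The only nearby mention of adjustment is "Multinomial logistic regression will be used to adjust for potential confounders". It closes the cost-effectiveness paragraph, lists no confounders and does not say which outcome it serves.

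For the primary outcome, the same section compares change in cognitive score "after adjusting for potential confounders (baseline cognitive score, age, sex, education, visual function, quality of life, depression, falls, social interaction, and physical activity"), and the Abstract promises results with and without adjustment for baseline score. Table 1 (Secondary outcomes) schedules all six secondary instruments at baseline and at years 1, 2 and 3.

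**The concern.** Subtracting the baseline is not the same as adjusting for it. When baseline and follow-up correlate at less than 1, change is negatively related to the starting value. A comparison of change therefore keeps variation that a baseline covariate would remove. The article states this adjustment for cognition. In the paragraph that follows it gives a model for falls in which change is the quantity compared and no baseline term appears.

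The Background lists effects on quality of life, falls, depression, social interaction and physical activity among the trial's aims. Read as printed, the scored outcomes among these would have wider confidence intervals than the data allow. Randomisation does not compensate, because none of the secondary instruments is a stratification factor: "Stratified randomisation will be done based on gender (male/female), age (below and above median), education level (below and above median), and baseline HMSE" are the factors named.

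**Working it through.** **Inputs from the Protocol article.** 380 per arm (Abstract). Two-sided 5% test, 90% power, 13% annual loss and a 29% effect size (Sample size), read here as 0.29 SD.

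**Assumed.** The correlation ρ between baseline and three-year score is not given, so a range is shown. No effect size is given for any secondary outcome, so 0.29, 0.25 and 0.20 SD of change are illustrative. Variances are taken as equal at baseline and follow-up.

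**1. The plan's own figure.** Per arm, n = 2(1.960 + 1.282)² / 0.29² = 250. Retention over three years is 0.87³ = 0.6585. 250 / 0.6585 gives 380 per arm, 760 in total, as stated. Conversely, 380 × 0.6585 leaves 250 per arm at 36 months.

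**2. Variance of the two analyses** (one baseline, one follow-up, in units of the outcome variance):

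- change compared alone: 2(1−ρ)
- follow-up adjusted for baseline: 1−ρ²
- ratio, adjusted to change: (1+ρ)/2, below 1 for every ρ below 1.

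The detectable difference at 90% power, in outcome SD, is (1.960 + 1.282) × √(2v/250), where v is the variance above.

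| ρ | Change 2(1−ρ) | Adjusted 1−ρ² | Ratio | Detectable, change | Detectable, adjusted |
|---|---|---|---|---|---|
| 0.3 | 1.40 | 0.91 | 0.65 | 0.343 | 0.276 |
| 0.5 | 1.00 | 0.75 | 0.75 | 0.290 | 0.251 |
| 0.7 | 0.60 | 0.51 | 0.85 | 0.224 | 0.207 |
| 0.8 | 0.40 | 0.36 | 0.90 | 0.183 | 0.174 |
| 0.9 | 0.20 | 0.19 | 0.95 | 0.130 | 0.126 |

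**3. Power at 250 per arm** (noncentral t). An effect of d SD of change becomes d/√((1+ρ)/2) after adjustment.

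| d (SD of change) | Change alone | Adjusted, ρ = 0.3 | Adjusted, ρ = 0.5 | Adjusted, ρ = 0.8 |
|---|---|---|---|---|
| 0.29 | 89.9% | 98.0% | 96.2% | 92.7% |
| 0.25 | 79.7% | 93.3% | 89.6% | 83.7% |
| 0.20 | 60.7% | 79.1% | 73.1% | 65.3% |

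**4. Chance imbalance.** Given an observed baseline difference b, the change contrast is shifted by (ρ−1)b. With b = 0.1 SD the shift is −0.07, −0.05 and −0.02 SD at ρ = 0.3, 0.5 and 0.8. This is not a further cost, because 2(1−ρ) = (1−ρ²) + (1−ρ)². The second term is the variance that this shift contributes; at ρ = 0.5 the sum is 1.00 = 0.75 + 0.25.

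**5. Does a mixed-effects model recover the gain?** Not by itself. If baseline is one of the repeated responses and the arm means are free at baseline, the 36-month contrast with complete data equals the difference in mean change. The gain requires baseline as a covariate, or arm means constrained to be equal at baseline. The article states neither.

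**The case against.** The strongest reply is that nothing in the article says the secondary analyses omit baseline. It is a condensed account, and covariate lists for secondary models are commonly left to a fuller plan. The authors also describe the primary outcome as change and still adjust it for baseline, so their use of the word does not imply an unadjusted comparison. This stands in part. A reader might infer that all six secondary outcomes are to be compared as unadjusted change scores, and the document does not support that. Depression has binomial models, physical activity and social interaction are categorised, and no between-group model is named for quality of life or visual functioning. Only falls has a stated linear model of change.

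A reader might also infer that the secondary comparisons are biased. They are not. Under randomisation the change contrast is unbiased on average, and its dependence on chance imbalance is already in its variance.

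The size of the gain is open to challenge too: ρ is assumed, the formulas cover a single follow-up of a continuous score, and at ρ = 0.9 only 5% of the variance is saved. That limits the size. The direction holds for any ρ below 1.

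The confounder sentence does not answer the point. Multinomial regression could at most serve the three-category outcomes, not the scored ones.

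**Conclusion.** The point holds for the secondary outcomes analysed as scores: Rasch-scored quality of life and visual functioning, and the falls score. For these the article defines the outcome as change and names no own-baseline covariate, and for falls it makes the difference in change the estimated quantity. It does name such a covariate for the primary outcome. Stating baseline adjustment is a better method using data already scheduled, so this is more than a request for detail.

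The saving is 25% of the variance at an assumed ρ of 0.5, ranging from 35% at 0.3 to 10% at 0.8. In power terms, for a difference of 0.25 SD of change, the gain is about 10 points at ρ = 0.5 (14 at 0.3, 4 at 0.8). These figures rest on 250 completers per arm, equal variances, one follow-up and illustrative effect sizes. They do not carry over to the binomial or three-category analyses. How far the point bites for quality of life and visual functioning depends on a model the article does not name. The primary analysis and the sample size of 760 are unaffected.

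**What to change.** In the secondary-outcome paragraph of Data management and analysis plan, state the following.

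- **Scored outcomes** (Rasch-scored quality of life and visual functioning, and the falls score): the follow-up values are the response. The model contains arm, visit, arm-by-visit, the instrument's own baseline score and the stratification factors (gender, age, education, baseline HMSE). The 36-month arm contrast is reported. It still estimates the between-group difference in change, with a smaller standard error.
- **Depression:** keep the stated relative risk and risk difference, and add the baseline value as a covariate where the model allows. Moving to a PHQ-9 score analysis would change what is estimated and is not proposed.
- **Physical activity and social interaction:** keep the three-category analyses, with the baseline value as a covariate where the model allows.

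The cost is a few sentences before database lock and a few degrees of freedom. No new data, visits or staff are needed.
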